## Abstract

**Introduction:**

Mental healthcare organisation can either pursue *specialisation*, that is, distinct clinicians and teams for inpatient and outpatient care or *personal continuity of care*, that is, the same primary clinician for a patient across the two settings. Little systematic research has compared these approaches. Existing studies subject have serious methodological shortcomings. Yet, costly reorganisations of services have been carried out in different European countries, inconsistently aiming to achieve specialisation or personal continuity of care. More reliable evidence is required on whether specialisation or continuity of care is more effective and cost-effective, and whether this varies for different patient groups and contexts.

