This study was funded by the 7th Framework Programme of the European Commission (Full title: Comparing policy, framework, structure, effectiveness and cost-effectiveness of functional and integrated systems of mental health care—COFI).

COFI will be the largest study comparing specialisation and personal continuity of care, reaching more patients than all of the previous studies combined. The study will involve a comprehensive assessment of outcomes, cost-effectiveness and patient/clinician experiences. It will include services in which specialisation or personal continuity approaches are the standard way of providing mental healthcare, rather than experimental programmes.

The comparison of the two approaches will be carried out in a wide range of settings, and in countries with different traditions and practices of mental healthcare. ‘Specialisation’ and ‘personal continuity’ approaches are supported in these different countries by a variety of funding mechanisms, policies and clinical arrangements. This will allow for the generalisability of our findings from the participating countries to a higher number of countries with similar characteristics.

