### Sample size determination

The sample size for the quantitative study was calculated with the aim to detect a 5% difference in rates of re-admissions (ie proportion of patients re-hospitalised during the one year follow up) between the two care approaches from 27.5% to 32.5% with 80% power at the 5% significance level.

The sample size required for an individual-level comparison not considering clustering of outcomes within centres and hospital would be 2716 patients.

We calculated an average cluster size per hospital of 150 patients recruited over one year. Taking into account a 15% drop out rate, the average number per hospital of patients recruited and followed up will be 128. The variance inflation factor (or design effect, IF) is given by IF=1+(m−1)×ρ; where m=cluster size, and ρ=ICC (inter-cluster correlation coefficient). The ICC in a cluster with such a large number of patients is expected to be very small.^37^ With m=128 and ρ=0.007, IF is 1.90, and the adjusted sample size is N=5162 (1034 per country), requiring eight hospitals per country with an average number of 150 patients recruited per hospital, ie 1200 patients per country and 6000 overall.

We will carry out follow-up face-to-face interviews with a subsample of patients who will be 18–65 years of age. The patients will be stratified based on diagnostic group (ICD codes: F20–29, F30–39, F40–49)^27^ and on whether the index admission was their first one or they have had previous hospital admissions. We will aim to interview 30 patients per stratum, resulting in 360 patients per country (60×6 clusters) and an overall sample of 1800 patients (360×5 countries).

For the in-depth interviews, we will purposively select 40 patients and 13 clinicians in each country, resulting in a total sample of 200 patients and 65 clinicians.

Within the sample, there will be a mix of: (1) patients treated with ‘specialisation’ and ‘personal continuity’ of care approaches; (2) those who were rehospitalised during the follow-up and those who were not; and (3) patients with different diagnoses (F20–29, F30–39, F40–49).

Clinicians will be included taking into account: (1) the care approach (‘specialisation’ or ‘personal continuity’) adopted by the service they work within and (2) their qualification: psychiatrists, psychologists, nurses/social workers.

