### Analysis of clinical and social outcomes

Mixed effects models with an unstructured variance matrix will be used to assess differences in the primary outcome (rehospitalisation), and in the other clinical and social outcomes between the two groups. We will explore random effects for the hospitals or ‘specialisation’ and ‘personal continuity’ of care clusters within the hospital (in Germany, Belgium and Poland), and use fixed effects for the following covariates:
Age, gender, diagnostic group, whether or not a patient has been previously admitted, severity of illness at baseline, social situation (SIX score) and formal status of the patient at baseline.

We will check the selection bias by comparing data of our sample with the aggregate data for the total group of admitted patients during the same period.

Potential mediators of effectiveness may be: (1) the intensity of treatment, that is, sum of inpatient days and outpatient visits; (2) the experience of hospital care within the index admission, which has been shown to be predictive of better outcomes following discharge.^38^
^39^ A higher intensity of treatment or a better experience of hospital care may occur in either the ‘specialisation’ or the ‘personal continuity’ of care approach and be responsible for better outcomes.^21^
^38^ We will develop a mediation model^40^ in order to identify and explicate a potential effect of intensity of treatment and/or experience of hospital care during the index admission for assessing the effectiveness of the two approaches.^41^

Exploratory analyses to compare clinical outcomes, social outcomes and untoward events between the ‘specialisation’ and ‘personal continuity’ of care approaches will also be carried out on subgroups of patients defined by:
Age (younger or older than 40 years);Gender (males or females);Primary psychiatric diagnosis (F20–29 or F30–39 or F40–49);First or repeated admission;Socioeconomic situation (receiving state benefits due to low income or not);Migrant status (ie, country of residence different from country of birth or not);Presence of physical comorbidity/comorbidities for substance use, diabetes, cardiovascular diseases or not.

All subgroup analyses will be performed by including the relevant variables as interaction terms in the models.

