## Discussion

COFI is a natural experiment which will overcome limitations of the currently available evidence:
It is a multicentre study carried out in countries with very different traditions, funding mechanisms and policies for mental healthcare. In all these countries, care approaches supporting either specialisation or personal continuity of care coexist. This will allow for comparisons to be made within a similar context and not be confounded by country-specific characteristics. The service arrangements supporting specialisation or personal continuity of care may vary substantially among the countries, which will make our findings more robust and increase their generalisability to other countries and contexts.It is powered to detect very small differences in clinical and social outcomes between the two care approaches assessed that are relevant from a policy decision-making point of view (eg, 5% in rates of rehospitalisation).A comprehensive range of outcomes will be assessed, encompassing clinical outcomes, social outcomes, safety of care indicators, patient satisfaction with services and cost-effectiveness.Care approaches supporting specialisation or personal continuity of care which are assessed in this study are already established as routine services and are not just pilot experimental services. This will be a methodological safeguard from the ‘novelty bias’ found in the existing literature in which the newly established approaches (either supporting specialisation or continuity of care) tend to have better outcomes than the traditional ones.^21^

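### Subgroup interactions are pooled over five countries with no approach-by-country term, so they can partly reflect country differences, and no country-specific effect on readmission is planned

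*Protocol article*

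**What the plan says.** Under Analysis of clinical and social outcomes, the protocol article gives the fixed effects (age, gender, diagnostic group, previous admission, severity, SIX score, formal status). The random effects to be explored are for hospitals or, in Germany, Belgium and Poland, for approach clusters within hospitals. It then lists seven exploratory subgroup variables: age, gender, diagnosis, first or repeated admission, benefits receipt, migrant status and physical comorbidity. For these it says: "All subgroup analyses will be performed by including the relevant variables as interaction terms in the models". Country appears neither as a covariate nor as a subgroup.

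Elsewhere the article describes countries as differing in ways that bear on the contrast. The Introduction says that the two approaches are "supported in these different countries by a variety of funding mechanisms, policies and clinical arrangements". Under Study design, allocation is by area in the UK and Italy, by clinical decision and patient choice in Belgium and Poland, and by insurance in Germany. The abstract says that evidence is needed on "whether this varies for different patient groups and contexts". The Discussion presents the variety of arrangements as something "which will make our findings more robust and increase their generalisability to other countries and contexts".

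**The concern.** An approach-by-patient-variable interaction pooled over countries mixes two things: a difference between patient groups within a country, and a difference between countries that happen to have more or fewer such patients. Benefits receipt and migrant status are obvious candidates for uneven distribution, since they depend on national benefit systems and populations. The approach contrast could differ by country because the services differ. It could also differ because selection into an approach works differently, even if the true effect is the same everywhere.

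The two hypotheses under Aims and objectives concern which patients suit which approach. A country difference could therefore be read as evidence for or against them. Separately, a pooled readmission effect could be generalised to other countries without the reader seeing whether it holds in each of the five.

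**Working it through.** **1. The plan's own figures.** The inputs are "from 27.5% to 32.5% with 80% power at the 5% significance level" (two-sided assumed). The standard two-proportion formula gives 1318 per arm. With the continuity correction, n' = (n/4)[1 + √(1 + 4/(n × 0.05))]² = 1358, so 2 × 1358 = 2716, which matches "not considering clustering of outcomes within centres and hospital would be 2716 patients". The design effect is 1 + 127 × 0.007 = 1.889. Then 2716 × 1.889 = 5131 and 2716 × 1.90 = 5160, against the stated 5162. The size is reproduced, and I use its layout: 5 countries, 8 clusters each, 128 followed up per cluster, base rate 30%.

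**2. Size of the leakage.** Let q be the subgroup share and d the approach effect in each country, with no true interaction. With equal-sized countries and no random effects, the expected interaction coefficient is

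bias = Cov(q, d) / [q̄(1 − q̄)].

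With a cluster random intercept, between-cluster information is down-weighted by ψ = (1 − ρ)/(1 − ρ + mρ). At ρ = 0.007 and m = 128, ψ = 0.993/1.889 = 0.526, and

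bias ≈ ψ Cov(q, d) / [mean q(1 − q) + ψ Var(q)].

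The article gives no shares or effects by country, so these scenarios are assumptions:

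- A: effect -10 points in one country and 0 elsewhere; share 60% there, 20% elsewhere.
- B: effects +5 to -5 points in equal steps; shares 10% to 50%.
- C: as A, with share 40% against 20%.
- D: effects +10 to -10 points; shares 20% to 80%.

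Example A: q̄ = 0.28 and mean d = -0.02, so Cov = -0.012 + 0.0056 = -0.0064. Without random effects the bias is -0.0064/0.2016 = -3.2 points. At ρ = 0.007 it is -0.00336/(0.176 + 0.0135) = -1.8 points.

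**3. Estimated cluster variance.** Fixing ρ at 0.007 overstates the bias, because the omitted country differences raise the estimated cluster variance, which then absorbs more. I therefore simulated binary outcomes (1500 replicates, linear mixed model, REML, true ρ 0.007), once with equal base rates and once with base rates of 20% to 40% across countries. Bias is in points; the percentage is the rejection rate.

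| | No random effects (formula) | ρ fixed at 0.007 (formula) | ρ estimated, equal base | ρ estimated, base 20–40% |
|---|---|---|---|---|
| A | -3.2 | -1.8 | -1.4; 7.8% | -0.5; 5.6% |
| B | -2.4 | -1.3 | -1.0; 7.0% | -0.5; 5.0% |
| C | -1.8 | -0.9 | -0.7; 5.3% | -0.2; 6.1% |
| D | -6.0 | -3.4 | -1.9; 11.3% | -1.7; 8.6% |

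The simulation error of a rejection rate is about 0.6 points near 5% and 0.8 near 10%. With random effects dropped and equal base rates, simulated rejection was 22.5%, 13.8%, 9.7% and 60.5% in A to D. If q and d are uncorrelated over countries, the covariance and hence the bias are 0.

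**4. Which term removes it.** Country main effects alone left -0.7 to -2.6 points (rejection 5.5% to 15.9%), because they also take away the between-country variance that the random intercept had been absorbing. Adding approach-by-country brought the bias to within 0.2 points of zero and rejection to 4.2–5.6%. The standard error rose by at most about 3% (A: 2.92 to 3.01 points). With ρ held at 0.007, the rise in D is 5.6% (2.66 to 2.81 points).

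**5. Precision of country effects.** Effective N = 5162/1.889 = 2733, or 547 per country. The standard error of a country's risk difference is √(4 × 0.21/547) = 3.9 points, so its 95% interval is about ±7.7 points. The 4-df heterogeneity test has noncentrality Σ(d − d̄)²/SE². Its power is 12% if one country differs by 5 points, 41% if one differs by 10, 33% for effects graded +5 to -5, and 92% for +10 to -10.

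**The case against.** The strongest reply is that this is detail of exploratory models that an article leaves to the full protocol or analysis plan. Part of that stands: the subgroup analyses are labelled exploratory, and an unseen plan could add the term. But this article sets out its covariates, random effects and subgroup variables, and country is in none of them.

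A reader might infer that a stated research question on contexts goes untested. The documents do not support that. The abstract's wording is background on what evidence is needed, and the questions under Aims and objectives include none on country or context. Nor is context ignored: Analysis of costs foresees cross-national comparisons, and the secondary analysis studies system characteristics and relates a continuity rating to outcomes. Neither, however, yields a country-specific approach effect on readmission.

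A reader might also infer that the subgroup results will be seriously misleading. That is not supported either. The leakage needs effect and subgroup mix to vary together over countries. The cluster random effects absorb much of it, and in several scenarios rejection stays close to 5%. The planned approach clusters within hospitals may carry some further heterogeneity. All country effects and shares here are assumed, and D, with a 20-point spread of effects, is extreme against the 5-point difference that the study is sized for.

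**Conclusion.** The point holds as a modest weakness of the stated model. With no true interaction and an estimated cluster variance, the assumed scenarios give a spurious subgroup interaction of about 0 to -2 points and rejection of about 4% to 12%. Without the random effects, which the text only promises to explore, the bias reaches about -6 points in the most extreme scenario. These figures rest on equal-sized countries, four clusters per approach in each, 128 patients per cluster, and assumed shares and effects by country. The primary pooled readmission comparison is not shown to be wrong. What is missing for it is a display of the effect by country to support the claim of wider generalisability. Severity is minor to moderate, and the improvement is cheap.

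**What to change.** In Analysis of clinical and social outcomes, add country and approach-by-country to every subgroup model, so that patient-group interactions are estimated within countries. For readmission, report the five country-specific approach effects with confidence intervals. Give the 4-df heterogeneity test only as supporting information, because its power is low for 5-point differences. Reword the generalisability statement in the Discussion so that it rests on the consistency of the country estimates and the width of their intervals; a non-significant test should not license it.

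The cost is wording and a few extra parameters (four for country, four for approach-by-country). The standard error of the subgroup interactions rises by roughly 1% to 4%, somewhat more only in the extreme scenario with ρ held at 0.007. No new data are needed.

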### Analysis of costs

The economic analysis will be led by the Centre for the Economics of Mental and Physical Health at King’s College London. Unit costs for each service measured with the CSRI will be calculated for each country. In order to compare costs across countries with different currencies, purchasing-power parities will be used to transform the country-specific costs into a single currency, thus allowing for analysis of the total sample as well as cross-national comparisons. The likely different impact of cost externalities or different cost structure of the two care approaches will be evaluated. Multiple regression will be used to adjust for the baseline patient characteristics in all tests of differences in costs and clinical outcomes. Cost-effectiveness will be then explored through the calculation of incremental cost-effectiveness ratios (ICER), defined as the difference in mean costs divided by difference in mean effects.

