## Data analysis plan

### Adjustment for confounders

The coexistence of the two care approaches in the five participating countries may be considered a major strength of the present study. Yet, clustering in outcomes may be found within hospitals and countries; therefore, we will explore random effects for hospitals as part of mixed regression models.

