### Analysis of experience of care

The analysis of patient satisfaction with care and perceived continuity of care measured through quantitative methods will follow similar procedures to those described in the ‘analysis of clinical and social outcomes’ paragraph.

Data from semistructured interviews with patients and clinicians will be audio taped and transcribed verbatim, ensuring the removal of any identifying information to maintain anonymity. Transcripts will be analysed through a thematic content analysis method.^42^ Study centres in each country will generate a list of emerging codes based on a line-by-line analysis of the first three interviews with patients and first two with clinicians in the respective country.^43^ Consistency of coding will be assessed across all centres. First, researchers at the Institute of Psychiatry and Neurology of Warsaw (IPIN) and at Queen Mary University of London (QMUL) will screen the databases containing the coding results of the first interviews in each centre and discuss any discrepancies with the relevant centre. Second, researchers from all centres will provide further verification and clarification of the meanings of the codes during a one-day workshop. Third, each partner will code two interviews with patients and two interviews with clinicians (conducted in English or translated into English), and researchers at IPIN and QMUL will assess the coded data for discrepancies. Separate codebooks will be developed for interviews with patients and with clinicians, and interviews will be coded based on these.

Codes will be categorised based on their English translations. To obtain meaningful themes, the emerging categories and codes will be organised and grouped. Researchers from all centres will verify the emerging categories and themes to ensure consistency across the data set. Descriptive counts of themes, categories and codes will be use to summarise the data set.

QMUL group is experienced in conducting qualitative analyses of data from different countries as they have already led previous similar studies in which IPIN was also involved.^44^
^45^

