### Secondary analysis based on continuity of care as a ‘continuum’

A wide variability of care arrangements may support specialisation of clinicians and teams or personal continuity of care. This may determine intragroup differences among the services included within the categories of ‘specialisation’ and ‘personal continuity’ of care approaches. For example, the presence of a ‘care coordinator’ may guarantee continuity of care even when there are two different primary clinicians in the hospital and in the community. On the other hand, even when patients have the same primary clinician in the hospital and in the community, they may be treated for short periods of time by ‘specialist services’ such as home-treatment teams, emergency wards or psychiatric intensive care units led by different primary clinicians.

We will investigate the variety of system characteristics that lead to the implementation of specialisation and personal continuity of care in the five participating countries. This part of the study will focus on the financial and healthcare governance mechanisms that support both care approaches and will be led by the University of Louvain.

To explore this in more depth, we will also develop an instrument assessing continuity of care as a continuum. We will use this instrument to identify and rate different care arrangements within the two alternative approaches.

The association between different levels of continuity of care and the outcomes will be tested through mixed models taking into account random effects at an hospital level and fixed effects of the same covariates described above for the primary analysis.

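### The cost section specifies multiple regression with no hospital term for tests of costs and clinical outcomes, whereas the clinical section specifies mixed models with hospital random effects

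*Protocol article*

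**What the plan says.** Analysis of costs gives one modelling sentence: "Multiple regression will be used to adjust for the baseline patient characteristics in all tests of differences in costs and clinical outcomes". The ICER is then defined as the difference in mean costs over the difference in mean effects. The section mentions no hospital effect or cluster-robust error and does not point to another section.

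Analysis of clinical and social outcomes reads "Mixed effects models with an unstructured variance matrix will be used to assess differences in the primary outcome (rehospitalisation"). The same sentence extends this model to the remaining clinical and social outcomes, and the next one adds "We will explore random effects for the hospitals or ‘specialisation’ and ‘personal continuity’ of care clusters within the hospital (in Germany, Belgium and Poland"). The general statement under Adjustment for confounders is "clustering in outcomes may be found within hospitals and countries; therefore, we will explore random effects for hospitals as part of mixed regression models".

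The two later sections tie themselves to that model. Analysis of experience of care "will follow similar procedures to those described in the ‘analysis of clinical and social outcomes’ paragraph". For the continuum analysis the wording is "tested through mixed models taking into account random effects at an hospital level and fixed effects of the same covariates described above for the primary", which again points to the clinical section.

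Sample size determination, with 128 followed-up patients per hospital and an ICC of 0.007, states "IF is 1.90, and the adjusted sample size is N=5162 (1034 per country").

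**The concern.** The cost sentence covers all tests of differences in clinical outcomes, so it overlaps the section that gives those outcomes a mixed model. Two modelling rules then apply to the same variables. Inpatient bed days show this plainly: they are listed both as a clinical outcome and as a cost component.

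The rule in the cost section adjusts for patient characteristics only. A regression of that kind without a hospital term treats patients of one hospital as independent. If they are positively correlated and the care approach is set by hospital, standard errors for the comparison come out too small, p-values too low and intervals too narrow. The cost comparison and the ICER are what would be at stake. The economic analysis is led by a separate centre, so an analyst could reasonably take this section's wording at face value.

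**Working it through.** **Inputs from the Protocol article.** Readmission 27.5% versus 32.5%, 80% power, 5% level (taken as two-sided), cluster size m = 128, ICC = 0.007, stated inflation factor 1.90, stated totals 2716 and 5162 (Sample size determination). Care approach set by hospital in the UK and Italy; both approaches possible in one hospital in Belgium, Germany and Poland (Establishing exposure).

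**1. Reproduce the plan's figures.**
- Per group without continuity correction: [1.96·√(2·0.30·0.70) + 0.842·√(0.275·0.725 + 0.325·0.675)]² / 0.05² = 1318 rounded up, total 2636.
- With continuity correction: 1358 per group, total 2716. This matches the plan.
- Inflation factor: 1 + 127 × 0.007 = 1.889 (plan: 1.90).
- Clustered total: 2716 × 1.889 = 5131, or 2716 × 1.90 = 5160 (plan: 5162). The small gap is rounding.

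**2. Effect of leaving out the hospital term.** If the true variance is D times the variance the model assumes, a nominal two-sided 5% test has actual type I error 2·[1 − Φ(1.96/√D)].

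At the plan's ICC of 0.007:

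| Situation | D | √D | Type I error |
|---|---|---|---|
| Exposure wholly at hospital level | 1.889 | 1.374 | 15.4% |
| Five countries, (a) | 0.4 × 1.889 + 0.6 × 0.993 = 1.351 | 1.162 | 9.2% |
| Clusters of 64, (b) | 1 + 63 × 0.007 = 1.441 | 1.200 | 10.3% |

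(a) assumes that the UK and Italy supply two-fifths of patients with the full design effect, and that elsewhere a pure hospital effect cancels between the two approaches, leaving D = 1 − 0.007 = 0.993.

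(b) assumes that the correlated unit is the approach group within a hospital, with 64 patients (half of 128). Strictly this describes the shared-hospital countries. Putting it together with the full effect in the UK and Italy gives D = 0.4 × 1.889 + 0.6 × 1.441 = 1.620 and a type I error of 12.4%, still between the other figures.

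**3. Unknown ICC for costs.** The article gives none. With m = 128 and hospital-level exposure:

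| Assumed ICC | D | Type I error |
|---|---|---|
| 0.001 | 1.127 | 6.5% |
| 0.007 (plan, readmission) | 1.889 | 15.4% |
| 0.02 | 3.54 | 29.8% |
| 0.05 | 7.35 | 47.0% |

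**The case against.** The strongest reply is that multiple regression is a generic term that can include a mixed model, and that the sentence is about covariate adjustment. The statement on hospital random effects stands at the head of the whole data analysis plan, before the clinical, cost and experience sections, so it can be read as covering costs. The article is condensed, and details of the economic model may sit in a fuller document that is not shown. All of this stands to the extent that a reader who infers a decision to use ordinary regression and ignore clustering goes beyond the text. The article never says so.

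It does not remove the point. Elsewhere the article says mixed when it means hospital effects, and the two sections that follow restate the model or refer to it. The general statement concerns clustering in outcomes, and the aims list outcomes, costs and experiences separately. What the cost section does state differs from the clinical section.

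Three further inferences are tempting but unsupported:
- **Costs cluster more strongly than readmission because of local prices.** Unit costs are calculated per country and converted by purchasing-power parities, so prices cannot create differences between hospitals within a country. Service use could, but no figure is given.
- **The omission of country is a fault peculiar to the cost section.** Country is not a listed covariate in the clinical section either.
- **The study will report two different readmission effects.** The ICER's effect measure is not named, so this is possible but not established.

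**Conclusion.** The point holds as an inconsistent and incomplete specification. The cost and clinical sections must be reconciled, because the cost section read literally omits a feature for which the sample size was inflated 1.9-fold.

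If no hospital term is fitted, and at the plan's ICC, the nominal 5% level becomes roughly 9 to 10% over the five-country design under descriptions (a) and (b), about 12% when the two are combined, and about 15% as the upper figure for hospital-level exposure. These results assume equal cluster sizes, a large-sample normal test, equal country shares and even splits within shared hospitals. For costs themselves the size is not known, and the 6.5% to 47% range rests on assumed ICCs.

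The primary analysis of readmission is fixed as a mixed model in its own section and is not affected.

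**What to change.** Amend the modelling sentence in Analysis of costs as follows:
- Estimate costs, and the effects used in the ICER, with the same hospital (or approach-within-hospital) clustering structure and the same covariates as in Analysis of clinical and social outcomes.
- Name the ICER's effect measure and express it as a risk or mean difference derived from a model consistent with the primary one. Readmission is binary, so if that model is logistic its odds ratio cannot serve directly as the denominator.
- Base uncertainty for costs and the ICER on a method that respects clustering, either model-based or cluster-robust, or a bootstrap of whole hospitals. A bootstrap should keep both approaches together where they share a hospital, and it must allow for small numbers. The planned minimum is four hospitals per approach per country, and resampling only four units gives a mean's variance that is too small by a factor of (4 − 1)/4 = 3/4.

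This is a change of wording plus slightly more analysis work, with no new data. The price is wider intervals for costs.
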